### 2.3.2 Known Potential Benefits

Dronabinol has been shown to have benefits for chronic pain in other diseases.  A reduction in chronic pain for adults with sickle cell disease could lead to reduced opioid use, improved quality of life, or both.  It could also lead to reduced hospital utilization.  Other THC containing agents have been associated with reduced markers of inflammation in other diseases and in murine models of sickle cell disease.  Reduced levels of inflammation could lead to reduce pain as well as reduced rates of vaso-occlusive pain crisis and possible reduced end organ damage.

### 2.3.3 Assessment of Potential Risks and Benefits

Given the high prevalence of cannabis use in sickle cell disease, it is important to evaluate both the potential benefits to pain and quality of life and the potential risks. This study could provide new insights into whether THC containing agents should be used by people with sickle cell disease. Should dronabinol prove efficacious for the improvement of pain or quality of life in people with sickle cell disease, or for the reduction of markers of inflammation, we will write an R01 proposal for a phase III multicenter study.  If dronabinol is associated with poor safety or tolerability, this will be important to patients and clinicians in considering if people with sickle cell disease should use other cannabis containing products. As chronic pain in sickle cell disease is one of the largest predictors of poor quality of life, this study is timely and addresses an important public health need.

# 3 Objectives and Endpoints

| OBJECTIVES | ENDPOINTS | JUSTIFICATION FOR ENDPOINTS |
| --- | --- | --- |
| Primary | | |
| Patient Reported Outcome Information System (PROMIS, a non-disease specific patient reported outcome survey system) pain impact score | Change from baseline to end of week 8 | The primary outcome is the PROMIS pain impact score, which assesses not only the severity of the pain but the impact of the pain on the participant’s daily living, a more relevant patient-centered outcome. PROMIS pain impact score has been validated as a onetime measure in people with SCD, and further has been validated to detect changes over in other diseases of chronic pain.^63,64^ |
| Secondary | | |
| Other Patient Reported Outcomes (ASCQ-Me survey domains for emotional impact, social impact, stiffness, and sleep) PROMIS domains for neuropathic pain, nociceptive pain, cognitive function, gastrointestinal distress and anxiety.^66^ LANSS, PD-B, C-SSRS | Change from baseline to end of week 8 | Patients will complete ASCQ-Me survey domains for emotional impact, social impact, stiffness, and sleep as well as Patient Reported Outcome Information System (PROMIS, a non-disease specific patient reported outcome survey system) domains for pain impact, neuropathic pain, nociceptive pain, cognitive function, gastrointestinal distress and anxiety.^66^ Patients will complete the Leed’s Assessment of Neuropathic Symptoms and Signs (LANSS_ at the beginning and end of study. LANSS is a validated scale of pain quality questions with a scale of 0-24 in which a score of 12 or more defines the presence of neuropathic pain which has been previously used to define neuropathic pain in patients with SCD.^67,68^ The Prodromal Questionaire - Brief is a short psychiatric survey validated to assess for early symptoms of psychosis and the Columbia Suicide Severity Rating Scale (C-SSRS) is a validated measure of suicidality.^59,60^ Both will be administered at each office visit. |
| Opioid Consumption in average daily oral morphine equivalents | Change from baseline to end of week 8 | Opioid use will be calculated using average daily morphine-milligram equivalents based on medications dispensed as documented in the New York State electronic prescribing monitoring program. |
| Laboratory Measures of Inflammation: WBC with differential, CRP, tryptase, substance P, VCAM-1 and cytokines IL1a, IL1b, IL6, IL4, IL10 and tumor necrosis factor alpha (TNFα) | Change from baseline to end of week 8 | SCD is complicated by chronic inflammation due to endothelial damage, ischemia-reperfusion injury, and hemolysis, and this can increase during VOC.^3,7,8^ Inflammation can cause pain directly and is also associated with worse disease severity in people with SCD. Substance P and tryptase are makers of pain sensitization in people with SCD (an experience of pain to lower levels of heat, cold, or pressure stimuli than average).^27,28^ Patients with SCD with greater levels of pain sensitization also have higher levels of pro-inflammatory cytokines IL1b, IL6, and TNFα release in response to painful stimuli.^29^ Substance P and the cytokine IL1b can also directly stimulate pain nerves to fire even in the absence of other stimuli (inflammatory pain).^30^ Both substance P, and tryptase as well as pro-inflammatory cytokines including IL1b, IL6, VCAM-1, and TNFα, have been shown to be elevated at baseline, while anti-inflammatory cytokines such as IL4 and IL10 are reduced at baseline, in people living with SCD, and these differences increase during pain crisis.^28,31^ Inflammatory mediators are not only correlated with pain sensitization and are involved in the development of pain crisis, elevated markers of inflammation such as high WBC and specifically neutrophilia are also associated with poor outcomes such as stroke or acute chest and increased risk of early mortality.^35,36^ Therefore, reducing inflammation in people with SCD may improve inflammatory pain and/or pain sensitization, but may also reduce disease morbidity and mortality.  Mouse models of SCD treated with CB1 and CB2 agonists had lower white blood cell count (WBC) and neutrophil count both at baseline and during pain crisis, reduced levels of tryptase, substance P and pro-inflammatory cytokines including interleukin (IL) IL1a, IL1b, IL6, and tumor necrosis factor alpha (TNFα). THC is a CB1 and CB2 partial agonists so would be expected to have similar effects, but this has not been studied. If THC reduces inflammation this may reduce pain directly, and additionally may reduce pain crisis frequency or SCD disease severity. |
| Tertiary/Exploratory | | |
| Analysis as above repeated examining patients with neuropathic pain only, and other pain types only, and patients who were cannabinoid naïve vs previous cannabinoid users, though these may be underpowered. | Change from baseline to end of week 8 | In a four-week open label study of dronabinol for patients with non-cancer chronic pain (nociceptive, neuropathic, and both), dronabinol was associated with a reduction in pain intensity and pain bothersomeness.^46^  In a study of over 600 patients with multiple sclerosis comparing dronabinol, oral cannabis, and placebo either dronabinol or oral cannabis were both associated with a reduction in pain compared to placebo and dronabinol was associated with fewer adverse effects compared to oral cannabis extract.^47^  Dronabinol may also have a benefit in pain sensitization.  Dronabinol reduces pain unpleasantness in studies of provoked pain, which may be explained by reduced processing between the sensory (pain severity) and limbic (emotional aspects of pain) areas of the brain seen in functional MRI studies.^48,49^ Thus, dronabinol may reduce pain impact by direct analgesic effect of nociceptive or neuropathic pain or by reducing pain sensitization and pain unpleasantness. |

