# 1 Protocol Summary

## 1.1 Synopsis

| **Title:** | Dronabinol for the reduction of chronic pain and inflammation in people with sickle cell disease |
| --- | --- |
| **Study Description:** | A randomized, double blind, study of dronabinol as a palliative agent in the treatment of pain, inflammation, and other complications of sickle cell disease (SCD). |
| **Objectives:** | \| Primary Objective: \| To determine whether dronabinol will improve pain and QOL in adults with SCD and chronic pain. \| \| --- \| --- \| \| Secondary Objectives: \| To assess dronabinol’s effect on markers of inflammation in patients with SCD compared to placebo.  To determine the safety and tolerability of dronabinol use in adults with SCD compared to placebo. \| |
| **Endpoints:** | \| Primary Endpoint: \| Change in PROMIS pain impact score \| \| --- \| --- \| \| Secondary Endpoints: \| - ASCQ-Me survey domains for emotional impact, social impact, stiffness, and sleep as well as Patient Reported Outcome Information System (PROMIS) domains for pain impact, neuropathic pain, and nociceptive pain and Leeds assessment of neuropathic signs and symptoms - WBC with differential, CRP, tryptase, substance P and cytokines IL1a, IL1b, IL6, IL4, IL10 and tumor necrosis factor alpha (TNFα). - Self-reported adverse effects, PROMIS domains for anxiety, appetite, nausea, and cognitive function, opioid use in oral morphine equivalents (OME), episodes of emergency room, hospital, or psychiatric facility utilization, Columbia suicide severity rating scale, prodromal questionnaire brief version \| |

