| 3 | 1,4 | survey | PQ-B and C-SSRS | X | | X | | X | | X | | X | |

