## 7.3 Lost to Follow-Up

**Retention strategy.** We will employ several strategies to maximize retention:

1.  Subject tracking. At all visits, we will record: 1) subjects’ address, phone numbers; 2) contact information of family or friends; and 3) locations where subjects work.

2.  Engaging subjects. Frequent contact with study staff helps to keep subjects engaged. As we have done previously, we will contact subjects by phone if they miss a questionnaire. In addition, we will hire study staff who are racial and ethnic minorities consistent with our source population to enhance mutual understanding and engagement.

3.  Subject compensation. To increase feasibility of attending each visit subjects will be compensated $25 per office visit and a two way metro card for cost of travel. Subject compensation will occur through study debit cards.

**Estimates and monitoring for attrition.** In this study, we conservatively estimate attrition of 20%. Retention reports will be included in reports to the DSMC every 6 months.

**Benchmarks and contingency plans.** We will conduct assessments every 6 months to verify benchmarks of: 90% retention rate. If benchmarks are not met, will institute contingency plans such as: adding or reserving more physician time for evaluations, better coordination between research and clinical staff, revising the incentive structure, or making other modification based on reasons for attrition.

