Urine toxicology tests will be performed at baseline and blood tests for cannabinoids at weeks 4 and weeks 8. Specimens will be labeled with the name of the research study, the date and time of collection, and the specimen number; no names or other identifying information will be used. The specimen number will be generated using the subject’s study ID number, the letters UT (to denote urine toxicology test), and the visit number. The laboratory will run toxicology tests for THC, methadone, opiates, cocaine, barbiturates, PCP, amphetamines, alcohol, and benzodiazepines on each specimen. The laboratory results will be available to [name] and the study assistant via the HIPAA compliant, encrypted, password protected clinical information system. They will not be reviewed until after the subject has completed the study to protect the masking.

We will conduct a blood test at screening and at weeks 4 and 8.  Laboratory markers of inflammation including IL1b, IL4, IL6, IL10, VCAM-1 and TNFα, tryptase, and substance P and safety laboratory tests of renal function, liver function, complete blood count and reticulocytes and pregnancy at screening and at weeks 4 and 8.

Assessments at weeks 2 and 6 are safety assessments only which consist of self reported adverse events, the PQ-B and the CSSR. These visits may be completed as in person or telemedicine visits.

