## 9.2 Sample Size Determination

In a study examining the responsiveness of PROMIS pain impact to changes in chronic pain patients who stated pain was a “little better” had an average increase of 1.8 point with a SD of 6.6 points and “much better” was associated with an average increase of 6.8 points with a SD of 6.5 points.^65^  Based on this we have chosen a change of 5 points as representing a clinically meaningful improvement in chronic pain, with an estimated a SD of 6.5 points. With a sample size of 28 patients (56 total) in each group we will have 80% power to detect a difference of 5 points in change between two groups in pain impact score from baseline at a two-sided 0.05 significance level.

We have a strong track record of following subjects with chronic pain, opioid use, and SCD in ourprior SCD studies have achieved 85-100% retention at 6 months. In our pilot trial we approached 27 patients to enroll 6 on study, we therefore estimate if we approach 280 patients, we can enroll 70. We conservatively estimate a 20% attrition rate, so we will aim to approach 280 patients to enroll 70 to ensure 56 participants completing the study.

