### 9.4.3 Analysis of the Secondary Endpoint(s)

To account for inter-patient heterogeneity, our primary comparison will be to use a difference in differences analysis to examine change from their own baseline after 8 weeks of treatment with dronabinol. Comparisons of changes in WBC with differential, CRP, tryptase, substance P, and cytokines from baseline to end of study between patients on placebo and dronabinol will be done using t-tests or Wilcoxon rank-sum tests. A backward stepwise multivariate regression analysis will be performed to assess for covariates associated with the primary and secondary outcomes. As the group size will be small a regression analysis will also be done to assess if any covariates associated with the outcomes are significantly difference between the study groups.

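### The PQ-B and C-SSRS endpoint uses only the week-8 change, so the stated arm comparison leaves out the scores at weeks 2, 4 and 6; a minor gap, cheaply closed by adding any-visit summaries

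*Protocol*

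**What the plan says.** Section 3 places both psychiatric scales in the same row as the pain and quality-of-life scores, with the endpoint "LANSS, PD-B, C-SSRS | Change from baseline to end of week 8". Section 9.4.3 says the main comparison for secondary endpoints is to "use a difference in differences analysis to examine change from their own baseline after 8 weeks of treatment with dronabinol".

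The synopsis (section 1.1) groups the two scales with the safety measures: "Columbia suicide severity rating scale, prodromal questionnaire brief version". Collection is more frequent than the endpoint needs:

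- Section 3: "Both will be administered at each office visit".
- Section 1.3, with columns for baseline and weeks 2, 4, 6 and 8: "PQ-B and C-SSRS | X | | X | | X | | X | | X".
- Section 8.1: "Assessments at weeks 2 and 6 are safety assessments only which consist of self reported adverse events, the PQ-B and the CSSR".

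Section 8.2 lists the psychiatric assessments at weeks 2, 4 and 8 only, which disagrees with sections 1.3 and 8.1 on week 6.

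Section 9.4.4 compares the arms on newly arising events, complaints and diagnoses. It names no scale score.

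**The concern.** A change at the end of treatment suits a benefit that should last. It suits less well a harm that can appear early and then resolve, or that leads to a lower dose, to stopping drug or to leaving. The week 2 and week 6 contacts exist for safety, and these two scales are most of what is collected there. Yet no sentence in the protocol carries those scores into a comparison between arms.

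Three kinds of participant show the difficulty. One whose score rose at week 2 and settled by week 8 counts as unchanged. One who stopped drug under section 7.1 but kept attending may be scored at week 8 off drug, although section 8.3.5 allows restart after some events. One who left before week 8 has no change score.

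Safety and tolerability are a stated objective. At stake is whether a null week-8 result on these scales could be taken to describe the whole 8 weeks.

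**Working it through.** **Inputs.** Enrolment of 70 and attrition of 20% are from section 9.2, which plans "to enroll 70 to ensure 56 participants completing the study". The alternative retention figure is from section 7.3: "We will conduct assessments every 6 months to verify benchmarks of: 90% retention rate". The four post-baseline assessments are from section 1.3. I assume that attrition means no week-8 score and that none is imputed.

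**The plan's own figure.** 70 × (1 − 0.20) = 56 completers, as stated.

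**Scores scheduled and used, per scale.** Scheduled post-baseline scores: 70 × 4 = 280.

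| Retention | Week-8 scores used | Share of 280 | No week-8 change |
|---|---|---|---|
| 80% (section 9.2) | 70 × 0.80 = 56 | 20% | 14 |
| 90% (section 7.3) | 70 × 0.90 = 63 | 22.5% | 7 |
| 100% | 70 | 25% | 0 |

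These are planning values. They measure data left out of the comparison, not bias.

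**What reaches the arms comparison by another route.**

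- Section 8.2 asks about new or worse symptoms at weeks 2, 4, 6 and 8, with a structured interview that includes paranoid thoughts and with open questions.
- Section 8.3.1 counts any unfavourable sign or symptom as an adverse event and sets no diagnostic threshold.
- Section 9.4.4 includes complaints as well as diagnoses, and section 9.3 takes everyone who had a dose.
- Psychotic symptoms are a stopping criterion (section 7.1), and the investigator reports the action taken with study drug because of an event (section 8.3.5). A symptom that leads to stopping should therefore be on the event record.
- Suicidal ideation triggers clinical intervention (section 8.2), so the C-SSRS loses less than the PQ-B. The protocol gives no PQ-B score that turns a rise into an event.

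**What is left.** To be lost, a rise must be scored on the scale, not be recorded as a complaint or event, and be gone, off drug or unmeasured by week 8. The protocol gives no rate for any of these steps.

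**Cost of an any-visit summary.** It depends on visits attended. Suppose one arm has 10 percentage points more participants seen once instead of four times.

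- PQ-B, assuming four exchangeable scores without ties: the single visit seen is the highest with chance 1/4. The share whose four-visit maximum is observed falls by 10 × (1 − 1/4) = 7.5 points.
- C-SSRS, assuming a proportion q worse than baseline at any one visit and independent visits: the any-time proportion is 1 − (1 − q)^4, and the fall is 0.10 × [1 − (1 − q)^4 − q].
  - q = 2%: 0.10 × (7.8% − 2%) = 0.6 points.
  - q = 5%: 0.10 × (18.5% − 5%) = 1.4 points (rounded up before display rounding of 18.5%).
  - q = 10%: 0.10 × (34.4% − 10%) = 2.4 points.
  - With fully correlated visits the fall is 0.

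**The case against.** The strongest case against is that little is lost. The event interview takes place at the same four visits and asks about the relevant symptoms, complaints are compared by arm, and symptoms that stop treatment should be recorded as events. Section 9.4.3 calls week-8 change the primary comparison, not the only one. Section 9.4.1 speaks of data from baseline to week 8, and section 9.4.8 lists every score by timepoint. A statistical analysis plan could add a worst-score summary. Using one visit of four is true of any endpoint fixed at a single visit, and the 14 without a week-8 score come from planned attrition.

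Most of this stands, and it is why the point is minor. It does not remove the point. Section 3 expressly fixes the timing for two safety scales, so this is a stated choice and not a detail left open. A listing is not a comparison, and no sentence uses the intermediate scale scores between arms.

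Two stronger readings are tempting. A reader might infer that early psychotic symptoms would go unseen in the arms comparison because they are unlikely to be recorded as adverse events. Nothing in the protocol supports that, and the interview content in section 8.2 points the other way. A reader might also infer a bias toward no difference. That would follow only if unrecorded rises tend to resolve or to end in stopping or leaving. If every rise lasts to week 8, there is none from this source.

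**Conclusion.** The concern holds in a limited form. The stated PQ-B and C-SSRS comparison uses one of four scheduled post-baseline scores: 20% to 25% of 280 per scale, with 14, 7 or 0 of 70 participants lacking a change score at 80%, 90% or full retention. The residual loss is scale rises, chiefly on the PQ-B, that are not reported as a complaint or event and are no longer visible, off drug or unmeasured at week 8. Its size cannot be computed from the protocol.

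Participant protection, the adverse event tables, the primary endpoint and the sample size are untouched. This is a cheap improvement to a secondary safety summary, not an error that threatens the trial. The counts rest on the planned enrolment and on attrition meaning no week-8 score.

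**What to change.** In section 3, keep week-8 change and add two summaries over weeks 2, 4, 6 and 8 in all dosed participants (the safety population of section 9.3), including values after stopping drug:

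- C-SSRS: the proportion per arm with any post-baseline ideation or behaviour worse than baseline.
- PQ-B: the maximum post-baseline increase.

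Give the arm difference with a 95% confidence interval for each; for the PQ-B a rank-based interval fits the non-normality assumption in section 9.4.1. Report the number of assessments per arm.

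The cost is wording, since all the data are already collected. The downside is the dependence on visits attended sized above: unequal early leaving can distort both summaries. Week-8 change and the assessment counts stay beside them for that reason. Participants who leave before week 2 are not recovered.

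Separately, add week 6 to the psychiatric assessment schedule in section 8.2 so that it agrees with sections 1.3 and 8.1.

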## 1.2 Schema

## 1.3 Schedule of Activities (SoA)

| **Related Aim** | **Related Skill** | **Form** | **Measure** | **Baseline** | | **Week 2** | | **Week 4** | | **Week 6** | | **Week 8** | |
| --- | --- | --- | --- | --- | --- | --- | --- | --- | --- | --- | --- | --- | --- |
| 1 | 1,2,4 | survey | PROMIS Pain Impact | X | |  | | X | |  | | X | |
| 1 | 1,2,4 | survey | ASCQ-Me Pain Impact | X | |  | | X | |  | | X | |
| 1 | 1,2,4 | survey | LANSS Scale | X | |  | |  | |  | | X | |
| 1 | 1,2,4 | survey | PROMIS Pain Quality Neuropathic | X | |  | | X | |  | | X | |
| 1 | 1,2,4 | survey | PROMIS Pain Quality Nociceptive | X | |  | | X | |  | | X | |
| 1 | 1,2,4 | EMR | Daily Opioid Use (OME) | X | |  | | X | |  | | X | |
| 1 | 1,2 | survey | Self Reported Episodes of Pain Crisis | X | |  | | X | |  | | X | |
| **Quality of Life Related Outcomes:** | | | | |  | |  | |  | |  | |  |
| 1 | 1,2 | survey | ASCQ-Me Stiffness | X | |  | | X | |  | | X | |
| 1 | 1,2 | survey | ASCQ-Me Sleep Impact | X | |  | | X | |  | | X | |
| 1 | 1,2 | survey | ASCQ-Me Emotional Impact | X | |  | | X | |  | | X | |
| 1 | 1,2 | survey | ASCQ-Me Social Impact | X | |  | | X | |  | | X | |
| **Inflammatory Markers:** | | | | | | |  | |  | |  | |  |
| 2 | 1,2,3 | blood | White Blood Cell Count | X | |  | | X | |  | | X | |
| 2 | 1,2,3 | blood | Absolute Neutrophil and Monocyte Count | X | |  | | X | |  | | X | |
| 2 | 1,2,3 | blood | Substance P | X | |  | | X | |  | | X | |
| 2 | 1,2,3 | blood | Tryptase |  | |  | |  | |  | |  | |
| 2 | 1,2,3 | blood | Pro Inflammatory: IL1-b, TNFα, IL-6, VCAM-1 | X | |  | | X | |  | | X | |
| 2 | 1,2,3 | blood | Anti Inflammatory: IL4, IL10 | X | |  | | X | |  | | X | |
| **Safety and Tolerability** | | | | |  | |  | |  | |  | |  |
| 3 | 1 | survey | PROMIS Anxiety | X | |  | | X | |  | | X | |
| 3 | 1 | survey | PROMIS GI Nausea and Vomiting | X | |  | | X | |  | | X | |
| 3 | 1 | survey | PROMIS Cognitive Function | X | |  | | X | |  | | X | |
| 3 | 1 | CRA | Self-Reported Adverse Effects | X | | X | | X | | X | | X | |
| 3 | 1 | EMR | Hospital Utilization (ER/Admissions) | X | |  | | X | |  | | X | |
| 3 | 1 | urine | Urine Pregnancy Test | X | |  | | X | |  | | X | |
| 3 | 1 | blood | BMP and liver tests | X | |  | | X | |  | | X | |
| **Other:** | | | | |  | |  | |  | |  | |  |
| 1 | 1 | urine | Urine Toxicology | X | |  | | X | |  | | X | |
| 1 | 1 | CRA | pill count | X | |  | | X | |  | | X | |

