# 8 Study Assessments and Procedures

## 8.1 Efficacy Assessments

Informed consent will be obtained prior to screening activities. Screening may take multiple visits but must be completed within 30 days of obtaining informed consent. The following assessments will be completed:

- Written Informed consent
- Demographics
- Medical history - Including SCD type, SCD related problems, other medical problems, psychiatric and substance use history, description of pain and pain treatment
- Weight
- Vital Signs
- Review of current and past medications
- Pregnancy test - For women of child bearing potential Urine or serum.
- Urine test for cannabinoids
- Physical exam
- Baseline Patient Reported Outcomes (ASCQ-Me survey domains for pain impact, emotional impact, social impact, stiffness, and sleep, PROMIS domains for pain impact, neuropathic pain, nociceptive pain, cognitive function, gastrointestinal distress and anxiety. LANSS, PQ-B, C-SSRS)

Data will be collected from five sources: 1) Validated patient reported outcome surveys at baseline, and weeks 4 and weeks 8; 2) Timeline Follow-Back for hospital utilization use at research visits at weeks 4 and 8; 3) medical interview and physical examination at screening, weeks 4 and weeks 8; 4) laboratory markers of inflammation including IL1b, IL4, IL6, IL10, VCAM-1 and TNFα, tryptase, and substance P at baseline, weeks 4 and weeks 8 5) urine toxicology tests at baseline and weeks 4 and weeks 8, 6) safety laboratory tests of renal function, liver function, complete blood count and reticulocytes and pregnancy at screening and at weeks 4 and weeks 8;

In-person screening research interview, screening medical interview and physical examination data will be recorded on paper data collection instruments that identify participants only by unique study ID number. Patient reported outcome surveys will be performed on an I-Pad and entered automatically into REDCap. Data will be entered into a password-protected, encrypted web-based REDCap database, and paper documents will be filed in a locked cabinet.

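### CRP and IL-1a are secondary endpoints, but no schedule or assay list in the protocol collects them; the tryptase and PROMIS appetite entries also need reconciling

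*Protocol*

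**What the plan says.** **Endpoints.** Section 3 lists the laboratory endpoints as "WBC with differential, CRP, tryptase, substance P, VCAM-1 and cytokines IL1a", followed by IL1b, IL6, IL4, IL10 and TNFα, each analysed as the change from baseline at week 8. The synopsis (1.1) has nearly the same list, without VCAM-1: "WBC with differential, CRP, tryptase, substance P and cytokines IL1a, IL1b, IL6, IL4, IL10", again with TNFα.

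**Analysis.** Section 9.4.3 plans "Comparisons of changes in WBC with differential, CRP, tryptase, substance P, and cytokines from baseline to end of study" between the arms. CRP and tryptase are named there. IL-1a is covered only by the general word cytokines.

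**Collection.** The SoA (1.3) has rows for white cell count, neutrophils and monocytes, substance P and tryptase, a row "Pro Inflammatory: IL1-b, TNFα, IL-6, VCAM-1", and a row for IL4 and IL10. All are marked at baseline, week 4 and week 8 except tryptase, which has no mark. Section 8.1 describes "laboratory markers of inflammation including IL1b, IL4, IL6, IL10, VCAM-1 and TNFα, tryptase, and substance P at baseline, weeks 4 and weeks 8", and a few paragraphs later repeats the same markers for screening and weeks 4 and 8.

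**Surveys.** The synopsis lists "PROMIS domains for anxiety, appetite, nausea, and cognitive function" among the safety endpoints. Section 3 instead has "PROMIS domains for neuropathic pain, nociceptive pain, cognitive function, gastrointestinal distress and anxiety".

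**The concern.** An endpoint defined as a change from baseline needs a baseline measurement. What is assayed, and at which visit, is fixed by the protocol's schedule; an analysis plan written later cannot supply a value that was never measured. Where a marker is in the endpoint list and the planned analysis but not in the schedule, the people ordering the assays and the people writing the analysis are working from different lists.

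Inflammation is the subject of a secondary objective. Section 2.3.3 also makes a reduction in inflammatory markers one of the results that would lead to a phase III proposal. Section 9.1 predicts a fall in all markers other than IL4 and IL10. Because the lists differ between sections, the set of markers covered by that hypothesis is not fixed.

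**Working it through.** No figure needs recomputing; the check is whether the lists agree. The disputed items, and VCAM-1 for comparison, compare as follows.

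| Item | Synopsis | Section 3 | SoA | Section 8.1 | Section 9.4.3 |
|---|---|---|---|---|---|
| CRP | endpoint | endpoint | no row | in neither list | named |
| IL-1a | endpoint | endpoint | not named in any row | in neither list | only if counted under cytokines |
| Tryptase | endpoint | endpoint | row, no visit marked | in both lists | named |
| VCAM-1 | not listed | endpoint | baseline, weeks 4 and 8 | in both lists | not named |
| PROMIS appetite | endpoint | not listed | no row | not listed | not named |

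**Count against the SoA.** Taking the white cell count and its differential as one item, section 3 has 11 markers. Eight have marked visits: white cells with differential, substance P, VCAM-1, IL1b, IL6, IL4, IL10 and TNFα. One has a row without marks (tryptase). Two have no entry (CRP, IL-1a). 8 + 1 + 2 = 11.

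**Count against 8.1.** The assay lists name eight of the 11: IL1b, IL4, IL6, IL10, VCAM-1, TNFα, tryptase and substance P. White cells are not in those lists but are covered by the blood count in the safety tests, which makes nine. The safety tests are kidney and liver function, blood count, reticulocytes and pregnancy, so they do not pick up CRP. 11 − 9 = 2, again CRP and IL-1a.

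**Result.** CRP and IL-1a, 2/11 = 18% of the section 3 markers, are the only two with no collection entry in either place. Splitting the white cell item into total, neutrophils and monocytes, as the SoA does, gives 2 of 13 (15%).

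**Tryptase.** The SoA leaves it unmarked, while 8.1 schedules it twice. Every other measure row in the SoA has marks. The blank row is therefore probably genuine, but marks lost when the table was converted to text cannot be excluded.

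**Appetite.** Section 3 and 8.1 agree with each other on gastrointestinal distress, and the SoA has a PROMIS row for nausea and vomiting. Only the synopsis mentions appetite.

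**The case against.** The strongest reply is that nothing need be lost. Section 3 itself gives CRP and IL-1a a baseline and a week 8 time point. Both lists in 8.1 are introduced by the word including, so they need not be exhaustive, and they already leave out the white cell count. Section 2.3.1 provides for about 30 cc of blood for safety tests and inflammatory markers at baseline, week 4 and week 8, so the visits and the draws exist.

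Much of this stands. The gap is in which assays are named, not in visits or blood. It does not close the gap: the white cell count is picked up by the SoA and by the safety blood count, whereas nothing that directs collection mentions CRP or IL-1a.

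The documents do not support several stronger readings that someone might infer:

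- *Tryptase would not be collected.* Section 8.1 schedules it twice. Only staff following the SoA alone would miss it.
- *Appetite is an endpoint left uncollected.* Section 3, 8.1 and the SoA all omit it, so a stray word in the synopsis is at least as likely.
- *Baseline is lost for all 70 participants.* That is a worst case. It requires that nobody act on section 3 or 9.4.3 and that no usable blood remain. The protocol text neither says that aliquots are kept nor rules it out.
- *The 8-week duration depends on CRP.* Section 4.2 uses CRP in acute infection only to illustrate that markers move over weeks, and it also cites the length of other studies.
- *VCAM-1 data are at risk.* It is in section 3, the SoA and 8.1. Its absence from the synopsis loses nothing, and 9.4.3 does not list its cytokines.

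**Conclusion.** The point holds for CRP and IL-1a. Two prespecified secondary markers of 11 are to be analysed as change from baseline, and no schedule or assay list in the protocol collects them. A site that follows the SoA and 8.1 would not assay them, and their baseline values could be lost. How many participants would be affected cannot be determined from the document.

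The tryptase row is a contradiction between the SoA and 8.1, subject to confirming the blank cells in the source table. Appetite is a mismatch between the synopsis and the rest of the protocol.

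The conclusion assumes that no laboratory manual or other operational document outside the protocol already adds the two assays. Even if one does, the protocol still disagrees with itself. The primary endpoint, its analysis and the sample size are unaffected. This should be corrected, ideally before baseline samples are processed.

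**What to change.** 1. Add CRP and IL-1a at baseline, week 4 and week 8 to the SoA and to both assay lists in 8.1, using the blood already drawn at those visits. Otherwise delete both from the synopsis and section 3, delete CRP from 9.4.3, and state there which cytokines are meant.
2. Mark tryptase in the SoA at baseline, week 4 and week 8, to agree with 8.1.
3. Delete appetite from the synopsis; or, if it is wanted, add it to section 3, the SoA and 8.1 with its visits.
4. While making these edits, use one marker list throughout, including VCAM-1 in the synopsis. This last item is tidying only.

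Keeping the two markers costs two extra assays on existing samples and some schedule wording. Dropping them costs wording only, and two fewer secondary markers. Keeping appetite would add a survey domain at each visit where it is scheduled. No change to visits or blood draws is needed.
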